### Measures

#### Mixed Methods Measures for Primary Outcomes: Intervention Feasibility Outcomes

Multiple forms of data will be collected within 12 weeks during the intervention for the intervention feasibility evaluation.

##### Feasibility, Acceptability, and Usability

Mixed methods will be used. Acceptability will be assessed using EMA on Likert items that rate how helpful the module is (1=not at all to 5=extremely). Usability will be measured using EMA on the Usefulness, Satisfaction, and Ease of use questionnaire [95], which assesses perceived usefulness, satisfaction, and ease of use for the module. At week 12, participants will join semistructured interviews measuring (1) feasibility, usability, and acceptability and (2) reactions to the content, format, concepts, visual presentation, assessments (survey and EMA), and adaptation to other platforms. The interview guide will be based on mHealth studies [97].

##### Engagement

Paradata on participants’ interactions with specific modules will be collected, including their frequency of reactions (ie, comments, “likes,” questions, and replies on specific posts) and personal posts to Instagram groups [37]. Retention will be assessed by calculating the percentage of participants engaging in the group at varying time points. Data will be collected in real time.

##### Dose of Intervention

Participants’ engagement in particular intervention modules will be measured in EMA surveys as guided by dose operationalization for mHealth interventions [98]. Dose for specific modules will be assessed in three domains (1 yes or no item each): (1) intervention actions (if viewing a post), (2) participant actions (if practicing a skill or completing an assignment), and (3) behavioral target actions (if adopting skills outside of the intervention).

#### Web-Based Surveys for Demographic Variables and Secondary Outcomes: Psychosocial and Behavioral Outcomes

The web-based surveys will measure demographic factors and psychosocial and behavioral factors outlined in the IMB-based conceptual model (Figure 2).

##### Demographic Characteristics

In the baseline preintervention survey, participants will be asked to report their background information regarding gender (ie, man, woman, transgender, or other), race or ethnicity (eg, White or African American or Black), age (y), socioeconomic status, education, family or household characteristics, and physical health status (Patient Health Questionnaire-15) [99].

##### NMUPO Measurement

The past–3-month NMUPO will be measured using relevant items from the Tobacco, Alcohol, Prescription medication, and other Substance use tool [100]. The scale includes 2 sections, with a screener followed by a brief assessment. The screener contains 1 item asking the frequency of NMUPO (ie, used just for feeling, more than prescribed, or without a prescription) with 5 response options (daily or almost daily, weekly, monthly, less than monthly, or never). Participants with a response other than “never” will be led to the brief assessment, including 3 dichotomous questions regarding their level of use, dependence, and concern from others related to the past–3-month NMUPO. The sum score of the brief assessment will be calculated, with a higher score indicating a greater level of NMUPO.

##### NMUPO Knowledge

Information about NMUPO and relevant topics, such as misconceptions, the role of fentanyl, naloxone, and xylazine, will be assessed using the NMUPO knowledge scale [61]. This scale will be developed according to the measure in POP4Teens and the formative study. This scale is proposed to include 15 statements related to opioids or NMUPO. Participants will be asked to determine if a statement is true or not (0=false and 1=true). Responses will then be rated by the research team, with higher scores indicating better knowledge of NMUPO.

##### Outcome Expectancies

Beliefs on positive or negative consequences of engaging in NMUPO will be assessed using a scale adapted from the Behaviors, Expectancies, Attitudes, and College Health Questionnaire [101]. A total of 50 items will be scored on a 5-point Likert-type scale ranging from 0 (not at all) to 4 (very often or always), with higher sum scores standing for the greater level of expectancies. The scale consists of 8 dimensions related to specific expectancies of opioids, including pain reduction, tension reduction, academic preference, emotion enhancement, social enhancement, guilt and dependence, cognitive impairment, and physical discomfort.

##### NMUPO Risk Perception

Perceived susceptibility and severity of engaging in NMUPO will be assessed using the Perceived Risk Scale for Prescription Drug Abuse [102]. This scale includes 5 items with 4 rating options (1=“strongly disagree” and 4=“strongly agree”). The sum score will be generated, with a higher score indicating a greater level of perception risk for NMUPO.

##### Action Self-Efficacy and Coping Self-Efficacy

Perceived control on making actions to stop or reduce NMUPO or confidence on coping with barriers against the actions will be assessed using an adapted version of the Self-Efficacy Scale [103]. A total of 6 items will be rated on a 5-point Likert scale (1=strongly disagree and 5=strongly agree) and can be organized into 2 subscales (coping self-efficacy and action self-efficacy) with 3 items each. The sum scores will be generated for each subscale, with higher scores indicating greater levels of self-efficacy.

##### Psychological Distress

Depression and anxiety symptoms in the past 2 weeks will be assessed using the Patient Health Questionnaire-9 [104] and Generalized Anxiety Disorder-7 [105], respectively. The Patient Health Questionnaire-9 is composed of 9 items asking the frequency of depressive mood experiences (eg, “feeling down, depressed, and hopeless”), while the Generalized Anxiety Disorder-7 comprises 7 items assessing the frequency of feelings of nervousness or worry (eg, “not being able to stop or control worrying”). Two scales have 4 response options ranging from 0 (not at all) to 4 (nearly every day). Sum scores for 2 scales will be generated, with higher scores indicating greater levels of depression or anxiety.

##### Resilience

The Connor-Davidson Resilience Scale will be used for assessing psychological resilience [106]. This scale has 25 items asking about personal capacities in response to stress, including tenacity, tolerance of negative affect, positive acceptance of change, and positive view of adversities. Items will be rated on a 5-point scale (1=not at all and 5=nearly all the time). The sum score will be generated, with a higher score indicating a greater level of resilience.

##### Other Substance Use

The engagement in the use of alcohol, illicit drugs, and cigarettes in the past 3 months will be assessed using the NIDA-Modified Alcohol, Smoking and Substance Involvement Screening Test [59]. The scale includes 12 dichotomous items (0=no and 1=yes) asking if a participant has engaged in using or misusing any of 12 individual substances.

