#### Participants and Recruitment

Participants for the formative study and intervention trial will be those who meet the following inclusion criteria: (1) aged between 18 and 25 years, (2) US residents, (3) engaged in NMUPO in the past 3 months, and (4) using Instagram at least 3 times a week in the past 3 months. NMUPO refers to the occurrence of the following behaviors (1 time or more): (1) taking a prescription opioid without a prescription, (2) taking more doses than prescribed, and (3) using opioid for a nonmedical reason (eg, getting high) [1-3]. Individuals will be excluded if they report (1) receiving substance use interventions in the past 3 months, (2) being diagnosed with SUD, or (3) not being proficient in English. We anticipate a total sample size of 100, with 30 for the formative study and 70 for the intervention trial.

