The entire recruitment procedure is presented in Figure 2. Recruitment will be conducted using two strategies: (1) peer outreach and (2) advertising campaigns. For the peer outreach approach, peer leaders will distribute recruitment advertisements via online social networking (eg, posting advertisements on their social media accounts and inviting subscribers to repost the advertisements). Peers can also send direct invitations to young adults who they personally know to be eligible for the study. For advertising campaign approaches, we will target the accounts (on Instagram or Facebook) of colleges, local young adult communities (eg, trade unions), and substance use support groups. Upon approval from their group administrators, we will post advertisements in the groups. In addition, we will develop targeted advertising using Ads Manager (Meta Platforms, Inc) [57]. The advertisements will display research-relevant images, hashtags, and headings, which are tailored to engaging content for young adults. To ensure appropriateness, the advertisements will be reviewed by a community advisory board. The advertisements for aim 3 will be improved in line with formative research. The Ads Manager will also determine the range of the advertisement campaign in terms of age, time, and locations (ie, the United States). The designed advertisements will be delivered in various formats dependent on the platforms, such as linear posts within personal feeds on Instagram, news feeds on Facebook, and stories on Snapchat. To ensure representativeness, recruitment will be stratified based on key demographics (eg, gender, race or ethnicity, and education) in line with the latest US national data on NMUPO [58]. The advertisements will navigate potential participants to a web-based sign-up survey on REDCap (Research Electronic Data Capture; Vanderbilt University), which is a secured web-based platform monitored by the University of South Carolina. The prescreening survey will include questions in terms of age, past–3-month NMUPO (National Institute on Drug Abuse [NIDA]–Modified Alcohol, Smoking and Substance Involvement Screening Test [59]), US residency, use of social media, and SUD diagnosis or treatment history. Participants who are identified as eligible will provide their preferred contact method (eg, Zoom [Zoom Communications, Inc]) in the survey for a brief preinterview online meeting with the study team for a fraudulent screening. Such a screening will be conducted by checking for inconsistencies in their responses, requesting time-stamped screenshots to prove their locations, and asking for information (eg, brand names) of prescription opioids that they have been using. Eligible participants with no fraud responses will then be invited to complete web-based informed consent. Young adults enrolled in the study will be provided with instructions for interviews (aim 1) or intervention (aim 3).

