##### Web-Based Pre- and Postintervention Surveys

The web-based pre- and postintervention surveys will be developed and administered on REDCap [94] to measure demographic variables as well as psychosocial and behavioral factors outlined in the IMB-based conceptual framework. Factors include NMUPO behaviors (past–3-month NMUPO) and information- and motivation-related factors (ie, NMUPO knowledge, NMUPO risk perception, outcome expectancies, self-efficacy, psychological distress, resilience, and other substance use). Web-based surveys will be conducted among participants in both the intervention and control groups. Participants will receive survey links via inbox messages to the Instagram accounts they provide for the study. The preintervention survey will be sent 2 weeks before the intervention (baseline), and the postintervention survey will be sent in the week immediately following the intervention (12-week follow-up). The survey will be self-administered and take approximately 20 to 30 minutes to complete. If participants cannot complete the surveys at one time, they can save their responses, and the platform will generate a code that allows them to resume the survey within the same week. The survey will also provide forward and back buttons, allowing participants to review and change their responses before they submit their surveys. Study IDs and filling time will be collected for determining duplicate entries. e-gift cards will be provided for the completion of surveys (baseline and 12 weeks; US $30 each).

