## Discussion

### Anticipated Findings

In response to the growing evidence on psychosocial aspects of opioid addiction and relevant disorder concerns in the United States, this proposed study aims to apply a psychosocial theoretical framework and peer role model techniques to develop and implement an evidence-based intervention for reducing NMUPO risk in young US adults. The intervention will be established through a serial research activity, from a formative semistructured in-depth interview study to feasibility evaluation of a 12-week interactive peer-led trial. By leveraging the merits of social media, the proposed intervention study will be powered by adopting innovative approaches, including a tailored recruitment strategy (eg, paid advertisement campaigns), intervention delivery that transcends time and space constraints, and the application of mixed methods and time-series assessments (eg, paradata and EMA measures). As one of the first attempts to deliver peer-led interventions on social media specifically targeting NMUPO, the findings from this mixed methods design will offer valuable insights into the use of innovative approaches for reducing opioid risk among young adults. In line with previous intervention studies for NMUPO on social media [45], we anticipate that our intervention will yield high feasibility outcomes. In particular, the mixed methods assessments for the intervention group will demonstrate (1) high feasibility, acceptability, and usability on all intervention modules among young adults across 12 weeks and (2) high engagement, especially for the modules in the interactive formats, such as discussion polls and live streaming group meetings. We also anticipate significant preliminary intervention efficacy on the NMUPO-related and psychosocial behavior outcomes. Compared to the control group, the intervention will report (1) decreases in past–3-month NMUPO and other substance use (eg, alcohol, illicit drugs, and cigarettes), (2) decreases in psychological distress, (3) changes in outcome expectancies (eg, increased physical discomfort and decreased pain reduction), (4) increases in NMUPO knowledge and NMUPO risk perception, and (5) increases in resilience and self-efficacy (ie, action and coping).

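### The other-substance-use outcome records only any use over about the whole treatment period, so it is largely insensitive to reduced use among regular users

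*Protocol article*

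**What the plan says.** Under Other Substance Use, the protocol article sets the construct and recall window: "The engagement in the use of alcohol, illicit drugs, and cigarettes in the past 3 months will be assessed". The response format follows: "The scale includes 12 dichotomous items (0=no and 1=yes) asking if a participant has engaged in using or misusing any of 12 individual substances". No frequency or quantity response is described.

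On timing, Web-Based Pre- and Postintervention Surveys states that "the postintervention survey will be sent in the week immediately following the intervention (12-week follow-up".

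The expected result appears under Anticipated Findings, where the intervention group is predicted to show, relative to control, "decreases in past–3-month NMUPO and other substance use (eg, alcohol, illicit drugs, and cigarettes".

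Two further places bear on the point. NMUPO Measurement uses a different instrument whose screener has five frequency levels, from daily or almost daily down to never. Participants and Recruitment uses the tool cited for other substance use at prescreening, to establish "past–3-month NMUPO (National Institute on Drug Abuse [NIDA]–Modified Alcohol, Smoking and Substance Involvement Screening Test [59", and past-3-month NMUPO is an inclusion criterion.

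**The concern.** The trial predicts that use of alcohol, illicit drugs and cigarettes will fall, but asks only whether each substance was used at all. Someone who goes from daily to monthly drinking answers yes both times.

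The recall window sharpens the problem. A 3-month look-back from the week after a 12-week programme reaches to about its first day. A participant who stops smoking completely in week 5 still truthfully answers yes. The programme puts information and motivation first and builds up behavioural skills later, so change that comes partway through is plausible, and this item would not record it.

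At stake is the reading of a secondary outcome. A real reduction among regular users could be reported as little or no difference and carried in that form into the planning of the larger trial. The insensitivity applies to both arms alike, so the risk is a missed signal rather than a spurious one.

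**Working it through.** The protocol gives no figure for this outcome, so there is none to reproduce. The check has three parts.

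**1. What an item can register.** On the five levels under NMUPO Measurement (daily or almost daily, weekly, monthly, less than monthly, never) there are four one-step reductions. A yes/no item separates only the last, less than monthly to never. The count describes the format; it does not say how likely each step is.

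**2. Sensitivity to a cut in frequency.** The protocol gives no baseline use rates, so these are assumed. If use follows a Poisson process with m expected occasions in the 12-week window, then P(item = 1) = 1 − exp(−m). A cut by fraction c replaces m with m(1 − c).

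| Assumed use | m | Before | 50% cut | 75% cut | 90% cut |
|---|---|---|---|---|---|
| Weekly | 12 | 1.000 | 0.998 | 0.950 | 0.699 |
| Monthly | 3 | 0.950 | 0.777 | 0.528 | 0.259 |
| Once per window | 1 | 0.632 | 0.393 | 0.221 | 0.095 |

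For example, a weekly user who halves use has m = 6, and 1 − exp(−6) = 0.998. In an arm of 35 such users, the expected fall in yes answers is 35 × (1.000 − 0.998) = 0.07 of a person. With 35 monthly users it is 35 × (0.950 − 0.777) = 6.1, and with 35 once-per-window users 35 × (0.632 − 0.393) = 8.4.

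A 75% cut from weekly leaves 12 × 0.25 = 3 occasions in 12 weeks, which is monthly use. The 5-level format would show that as a one-level drop, while the yes/no item moves only from 1.000 to 0.950.

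**3. Power for one any-use item.** The planned size is 35 per arm. At 75% retention, the lower end of the range cited under Power Analysis, about 26 remain (35 × 0.75 = 26.25). Two-sided alpha of 0.05 and the proportions are assumptions.

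| Control vs intervention | 35 per arm | 26 per arm |
|---|---|---|
| 50% vs 40% | 0.13 | 0.11 |
| 50% vs 30% | 0.40 | 0.31 |
| 50% vs 20% | 0.76 | 0.63 |

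Only a large difference in full-window abstinence would have a reasonable chance of showing on a single item.

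**The case against.** A reader might infer that the outcome cannot show a decrease at all. The documents do not support that. An item can go from 1 to 0, and the share of users or the number of substances endorsed can fall. Anticipated Findings does not say that the decrease means frequency, and Other Substance Use frames the construct as engagement in use, so a fall in the share engaging would satisfy both. The calculation agrees: reduction in infrequent users is visible. Near-blindness applies to regular users who cut down without stopping, and the protocol does not say how many participants those will be. People diagnosed with substance use disorder are excluded.

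A reader might also infer that the outcome counts NMUPO twice, because the same tool screens for it. That is possible but not established. The 12 substances are not listed, the heading says other substance use, and the NMUPO outcome has its own instrument. If an opioid item were kept, essentially every participant would score 1 on it at baseline by eligibility, and any fall would repeat the NMUPO result. A value fixed equally in both arms would not by itself bias the comparison.

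Nor does the goal-setting module show that partial reduction in other substances is the expected effect, since its goals concern NMUPO only. Finally, the pilot's primary outcomes are feasibility, usability and acceptability.

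All of this stands and limits the point. What it does not answer is the mismatch between an any-use item with a treatment-length recall window and a predicted decrease, when the protocol already uses a frequency format elsewhere.

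**Conclusion.** The point holds as one about sensitivity. The items register essentially only abstinence from a substance across about the whole treatment period, and they are largely insensitive to reduced frequency among regular users. This fits poorly with the decreases anticipated against control.

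The format and the timing come straight from the protocol. The size rests on assumed use rates and a Poisson pattern: almost nothing is seen when weekly users halve their use (1.000 to 0.998), and a good deal is seen when use is about once per window (0.632 to 0.393). Overlap with NMUPO is something to confirm and is not a finding of error.

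This is a minor-to-moderate weakness in one secondary outcome of a feasibility pilot. No primary conclusion depends on it.

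**What to change.** At baseline and 12 weeks, collect a frequency response for alcohol, cigarettes and illicit drugs, for example the five levels already used under NMUPO Measurement. Analyse frequency, and keep any use as a derived binary summary (never versus any other answer), so nothing in the present measure is lost. State in the same place that any prescription-opioid item is left out of the other-substance-use score.

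The cost is a slightly longer survey and a response format that departs from the one now described for this tool. Five levels will still miss small changes within a category. Timing is favourable: the aim 3 protocol is due for ethics review in early 2027 and trial recruitment in late 2027, so no data are affected. Once baseline has been collected as yes/no, frequency cannot be recovered.

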### Data Analysis

The intervention trial will use multiple data analytic methods according to the format of the data.

#### Qualitative Analyses

Postintervention interviews will be audio recorded, transcribed, and coded using a pragmatic approach. The framework analysis [63] will be performed via a deductive process, including five key steps: (1) familiarizing the data, (2) developing a coding scheme, (3) condensing and structuring the data, (4) rearranging the coded data and comparing patterns, and (5) mapping and interpretating [64]. A codebook will be developed based on step 2 as a guide for coding. Coding disagreements will be resolved through group discussion. Data analysis will be conducted by the PI and graduate assistants on NVivo (version 11.0). Interrater reliability will be assessed throughout the coding process with a goal of ≥0.80 [65]. Analyses for postintervention interviews will synthesize the comments on feasibility, acceptability, and usability of the intervention, as well as summarize suggestions for improvements.

#### Quantitative Analyses

##### Bivariate Analyses

Data of web-based surveys (ie, before and after intervention) will be screened for missing data, outliers, and normality. If data are not missing (completely) at random or have a high missing rate (>5%), multiple imputation will be used [107]. Transformations will be conducted if violating normality (square root for moderate skew or log for greater skew). Attrition tests will be used (ie, chi-square tests and ANOVA) on demographics and outcomes at baseline. Descriptive statistics will be reported on primary (feasibility outcomes) and secondary outcomes (psychosocial and behavioral outcomes).

